### Demographics

A questionnaire to assess demographic information will be completed by each participant on the day of recruitment and include questions on age, educational level, marital and socioeconomic status, and length of time they have known about their HIV status.

### Data management and entry

All measurements will be entered on forms specifically designed for the project. Due to the number of measurements, forms of different colours will be used for easy identification. Completed forms will be checked for completeness by the PI or any other NISIR project staff present at the clinic. Each clinic will maintain separate files with all files stored safely by the PI.

Clinical assessment data including micronutrient analysis and socio-demographic assessment will be entered using EPI-INFO software (Centres for Disease Control and Prevention, Atlanta GA) while BIA, skinfold thickness, circumference and TBW measurements will be entered in Excel data sheets. Dietary intake forms will be checked for completeness by the supervisors at NFNC. A spread sheet in Excel 2007 will be created in which raw data from the record forms consisting of the foods and amounts consumed will be entered. Data bases containing nutrients to be used in the analysis will be created using food composition tables for Zambia [18], Food and Agriculture Organisation [19] and Mali [20,21]. Recipe databases will be created using values from the 2009 NFNC study and the Uganda/HarvestPlus databases. Then the data base containing nutrients from the food composition tables will be merged with those containing the foods and amounts consumed to calculate the nutrient intake.

### Sample size calculation

The sample size calculations were based on detecting a 5% weight change between groups over the 12-month period. Assuming a 10% variance in the within-group body weight, 37 participants are needed in each group to detect this difference with an alpha of 0.05 and a power of 90%. If the attrition is 25% over the year, a minimum of 48 participants are required in each group. Assuming FFM is 35% of the weight gain [22], 44 participants are needed in each group to detect this difference with an alpha of 0.05 and a power of 90%. If the attrition is 25% over the year, a minimum of 58 participants are required in each group. It is uncertain what magnitude of change is expected in CD4 counts and viral load. For a moderate effect size (Cohen's d = 0.4) 66 participants are needed in each group to detect this difference with an alpha of 0.05 and a power of 90%. If the attrition is 25% over the year, a minimum of 88 participants are required in each group.

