### Allocation to study groups

On the day of recruitment (baseline) after completing all body composition assessments and physical examination, the sister-in- charge will cut pieces of papers, equal to the number of participants enrolled that day. Half of the papers will bear the word 'Soya' while the other half will have 'No Soya' written on them. The papers will be folded several times to conceal the writing and then mixed. Each participant will be asked to pick one and read loud for the sister-in-charge to record the group assignment in the study registry book.

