Quality control will be done in accordance with the IAEA guidelines [15]. The equation proposed by the IAEA for use as a quality control measure in TBW (kg) = 7.4 × height^3 ^(m^3^), where TBW from each post-dose sample is used with the height of each participant. Since this equation will not be derived from our population in particular, a range incorporating the 95% confidence interval for the above relationship (< 5.7 × height^3 ^or > 9.6 × height^3^) also proposed by the IAEA for assessment of accuracy, will be considered. The TBW samples falling outside this range will be excluded from the analysis. The variation in TBW values depends on both the degree of analytical precision and natural biological variation.

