### Statistical Analysis plan

Statistical analyses will be performed using SAS software (SAS Institute, Cary, NC, USA). Descriptive statistics will be provided for the nutritional status, body composition, clinical and socio-demographic characteristics of the participants at baseline, 4, 8 and 12 months follow-up. At baseline, the characteristics of participants on food supplement and those without food supplement will be compared using t-test for continuous variables and Fisher's Exact Test for categorical variables. Repeated measures analysis of variance (RM-ANOVA) will be employed to compare the primary outcome variables (nutritional status and body composition) in participants with and without food supplements. Where confounding variables may need to be account for, adjustment will be made by covariance.

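### The 44 per group said to give 90% power for fat-free mass does not follow from the stated inputs, and no standard deviation for fat-free mass is given

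*Protocol article*

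**What the plan says.** The Sample size calculation section of the protocol article opens with the weight target: "The sample size calculations were based on detecting a 5% weight change between groups over the 12-month period". It then gives its one measure of spread: "Assuming a 10% variance in the within-group body weight, 37 participants are needed in each group". For FFM it adds one assumption and one result: "Assuming FFM is 35% of the weight gain [22], 44 participants are needed in each group to detect this difference", again "with an alpha of 0.05 and a power of 90"%. With 25% attrition it asks for 58 per group. No SD is stated for FFM or for its change over 12 months, and neither the test nor its sidedness is named.

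The design has two parallel arms in equal numbers: "Half of the papers will bear the word 'Soya' while the other half will have 'No Soya' written on them". The Statistical Analysis plan section uses repeated measures ANOVA to "compare the primary outcome variables (nutritional status and body composition) in participants with and without food supplements". Body composition is therefore a primary outcome, and the comparison is between groups.

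**The concern.** If lean tissue is 35% of the gain, the FFM difference is about a third of the weight difference. Against an unchanged spread, a third of the effect needs roughly eight times the sample (1/0.35² = 8.2). The requirement instead moves only from 37 to 44. A much smaller SD must have been used for FFM, and the section does not say what it was or where it came from.

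The 35% describes how a mean gain divides between lean and fat tissue. It scales the effect. It says nothing about how much FFM, or FFM change, varies between women, so it cannot justify an SD of 35% of the weight SD.

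This matters because deuterium-derived FFM is central to the trial's aim. If the true SD is larger than the hidden one, a non-significant FFM result could be taken to mean that the supplement adds no lean mass, when the trial had little chance of detecting the lean gain it assumes.

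**Working it through.** **Inputs (Sample size calculation section)**
- Weight effect: 5%.
- Spread: 10% of body weight. It is labelled a variance but read here as an SD, so d = 5/10 = 0.5 for weight.
- FFM effect: 0.35 × 5% = 1.75% of body weight.
- Alpha 0.05 (two-sided taken), power 90%.
- FFM SD: not stated.

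**Formulas (normal approximation)**
- Two groups: n per group = 2(1.960 + 1.282)²/d² = 21.01/d².
- One sample or paired: n = (1.960 + 1.282)²/d² = 10.51/d².
- The t-test versions are solved numerically.

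**Step 1. Can 44 be reproduced from the stated inputs?** d = 1.75/10 = 0.175.
- Two-sample: 21.01/0.175² gives 687 per group (560 one-sided).
- One-sample: 344 by the normal formula, about 345 by the t-test (about 280 one-sided).
- If the 10% is taken literally as a variance, SD = √10 = 3.16%. FFM then needs 69 (two-sample) or 35 (one-sample), and weight needs 9 or 5 against the stated 37.

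None of these is 44.

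**Step 2. What does give 44?** The figure fixes only the ratio of effect to SD, and only once a test is chosen.
- One-sample or paired t-test, two-sided: n = 43.995 at d = 0.5, so SD = 1.75/0.5 = 3.5% of body weight. This equals 0.35 × 10%.
- Two-sample t-test, two-sided: 44 per group needs d = 0.699, so SD = 1.75/0.699 = 2.5% of body weight.

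**Step 3. Do the neighbouring lines identify the formula?** Only in part. The CD4 and viral load line (d = 0.4, 66 per group) fits the one-sample normal formula (10.51/0.16, i.e. 66). The two-sample formula gives 132 and the one-sample t-test gives 68. The weight line (37) fits neither two-sided version at d = 0.5: the one-sample t-test would again give 44 and the two-sample formula 85. It is close to a one-sided one-sample test (35 to 36).

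**Step 4. What if only the test formula is corrected?** Keeping d = 0.5, the two-sample t-test gives 86 per group, and 44 per group has 64% power. At 75 to 80 completers per group power is 86 to 88%. FFM then looks nearly adequate, but the unsupported 3.5% SD is still in place.

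**Step 5. How far does the answer depend on the missing SD?** Assumed FFM SDs, 1.75% effect, two-sided two-sample comparison (n by the normal formula, power by the t-test). The 75 is 100 per arm less the 25% attrition used in the section. The 80 uses the 20% drop-out given under Dietary intake study.

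| FFM SD, % of body weight | d | n per group for 90% | Power at 44 | Power at 75 | Power at 80 |
|---|---|---|---|---|---|
| 2.5 | 0.70 | 43 | 90% | 99% | 99% |
| 3.5 | 0.50 | 85 | 64% | 86% | 88% |
| 5 | 0.35 | 172 | 37% | 57% | 59% |
| 10 | 0.175 | 687 | 13% | 19% | 20% |

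**Step 6. Detectable difference.** At 75 per group, 90% power needs a difference of 0.533 SD of the analysed FFM measure. For the assumed 1.75% effect to meet this, that SD must be no more than 1.75/0.533 = 3.3% of body weight.

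**The case against.** Four points can be made for the plan.

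**The SD may be a change-score or baseline-adjusted SD.** The section speaks of change over 12 months, and FFM is measured repeatedly in the same women. With a high baseline correlation r, the working SD shrinks by √(1 − r²). For example, take an FFM SD of 10% of FFM, FFM at 65 to 80% of body weight and r = 0.95, all of them assumptions. Two-sample power at 44 per group is then 90 to 98%. This stands. A reader might infer that the 90% fails under every test formula, but with the SD unstated that cannot be shown.

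**The route to 44 is a reconstruction.** A reader might also infer that 44 can arise only by cutting the weight SD to 35%. It cannot be pinned down in that way. A two-sample test with an SD near 2.5% of body weight gives 44 as well, and the one-sample t-test that gives 43.995 reproduces neither 37 nor 66. Scaling both effect and SD by 35% would also leave FFM with the same d, and so the same n, as weight, yet the section prints different numbers. The scaling is consistent with 44 but not proved.

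**The total body water limits do not settle it.** The Determination of TBW section sets "a range incorporating the 95% confidence interval for the above relationship (< 5.7 × height^3 ^or > 9.6 × height^3"), and it is tempting to turn these limits into an FFM SD that contradicts 44. They are an external quality-control range around a height equation that, as the section itself says, does not come from this population. They give no SD of FFM or of FFM change in these women.

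**FFM does not set the enrolment.** The trial recruits 200, well above 2 × 58, and the largest stated need is 88 per group. This also stands. It limits the harm if the SD is small, but not if it is 5% or more.

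The article condenses a fuller plan and cites a source for the 35%. That source is invoked for the share of gain, however, and the article states 44 and 90% as results. They can be checked against the inputs printed beside them and do not follow.

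**Conclusion.** The point holds in this form: the stated 44 per group (58 with attrition) at 90% power for FFM is not reproducible from the section's inputs, which give about 687 per group (two-sample) or 345 (one-sample), and no FFM SD is given that would support it. The closest match, a one-sample t-test at d = 0.5, implies an SD of 3.5% of body weight. The 35% share of gain does not justify that SD, and it would survive a correction of the test formula alone.

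The actual power for FFM is unknown rather than shown to be low. At 44 per group it runs from about 90% to 13%, and at 75 per group from 99% to 19%, over assumed SDs of 2.5% to 10% of body weight. These figures assume a two-sided test, the 10% read as an SD, and an effect of 1.75% of body weight. A baseline correlation enters only through the SD chosen. The matter should be corrected because body composition is a primary outcome, but it does not call for a larger trial.

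**What to change.** In the Sample size calculation section, replace the FFM sentence and its 44 and 58 with a two-group calculation that states:
- the FFM effect, in kg or as 1.75% of body weight;
- an SD belonging to FFM or to 12-month FFM change, with its source, and not the weight SD multiplied by 35%;
- any baseline correlation assumed, and the sidedness of the test.

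Keep 200 women. Restate either the FFM power at the expected completers or the detectable difference, which is 0.53 SD of the analysed FFM measure at 75 per group and 90% power. In the Statistical Analysis plan section, specify that the FFM comparison is adjusted for baseline FFM, so that the analysis matches the SD used. Add that a non-significant FFM result will be interpreted from its confidence interval and not as absence of lean gain.

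The cost is rewording, with no extra participants or procedures. The downside is that the stated FFM power may be less favourable than 90%.

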A total of 200 participants will be recruited for the study and a drop-out rate of 20% is anticipated. Accordingly, we anticipate that dietary intake data will be collected from approximately 160 participants. Each field staff member will be assigned 2 participants per day therefore we anticipate that data collection will take about two months to complete. Each participant will be contacted a week before data collection to remind them of the visit by field staff. Wherever possible, an understanding of level of literacy will be established beforehand. For participants who are unable to read and write, somebody in the household will need to be identified to record for them.

Field staff will train two participants per day, one in the morning and the second in the afternoon. This will be done on Mondays while Tuesday, Thursday and Saturday (or Sunday for Seventh Day Adventists) will be the 3 days during which the participants will be recording their food intake. On the second day (Wednesdays) the field staff will visit the participant's home to conduct a 24-h dietary recall. This will be done to assess the correct observance of the diet records, after keeping the record for one week day. The results of which will be immediately compared with those recorded for one day and will be the basis for reinforcing what will be discussed during the training. All forms and the food scales will be collected on Sundays, or Mondays for Seventh Day Adventists. Five supervisors will pay random visits to participant's homes to check on the accuracy and completeness of recording.

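### The 66 per group stated for Cohen's d = 0.4 is half of what a two-group comparison needs; the planned 200 women give about 68–71% power for CD4 and viral load, not 90%

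*Protocol article*

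**What the plan says.** The Sample size calculation section of the protocol article gives three requirements, each at alpha 0.05 and 90% power and each inflated for 25% attrition.

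- **Weight.** The target is "detecting a 5% weight change between groups over the 12-month period". With a within-group variance given as 10%, "37 participants are needed in each group to detect this difference with an alpha of 0.05 and a power of 90" per cent. After attrition, "a minimum of 48 participants are required in each group".
- **Fat-free mass (FFM).** FFM is taken as 35% of the weight gain, which leads to 44 per group. After attrition, "a minimum of 58 participants are required in each group". No SD for FFM is given.
- **CD4 and viral load.** The size of change is described as uncertain, so a conventional effect is used: "For a moderate effect size (Cohen's d = 0.4) 66 participants are needed in each group". After attrition this becomes 88.

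The section states neither sidedness nor a within-person correlation. The abstract and the Dietary intake study section give a total of 200 women. The Allocation to study groups section describes an even split, so about 100 per arm. The Statistical Analysis plan section compares women with and without the supplement by repeated measures ANOVA, and names nutritional status and body composition as the primary outcome variables.

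**The concern.** The CD4 and viral load line gives everything needed to check it except sidedness, and the check fails by a factor of two. The design has two parallel arms and the effect is a standardised difference, yet 66 is the number that a single-group or before-and-after test would need. That test asks whether one group changes. The trial asks whether two groups differ.

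At stake is how the CD4 and viral load results are interpreted. A reader of the protocol would take 200 women as comfortably above the 88 per group stated, and so as giving more than 90% power at d = 0.4. The real figure is about 70%. A non-significant result would then carry less information than the protocol implies.

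**Working it through.** **Inputs.** From Sample size calculation: alpha 0.05 (taken as two-sided), power 90%, d = 0.4 for CD4 and viral load, a 5% weight difference with 10% variability, FFM as 35% of weight gain, and 25% attrition. From the abstract, Allocation to study groups and Dietary intake study: 200 women, split 1:1, and a 20% drop-out rate used there. The multiplier is (1.960 + 1.2816)² = 10.507.

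**Reproducing 66.** The one-sample or paired formula is n = 10.507/d². At d = 0.4 this is 10.507/0.16 = 65.7, so 66. This matches the plan's figure.

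**Two-group requirement at d = 0.4.**
- Normal approximation: n = 2 × 10.507/0.16 = 131.3, so 132 per group. The t-based calculation gives 132.3, so 133.
- After 25% attrition: 133/0.75 = 177.3, so 178 per group.
- More lenient readings do not reach 66. One-sided at 90% power needs 108, and two-sided at 80% power needs 100 (t-based 99.1).

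**Power at d = 0.4.** The approximation is Φ(d√(n/2) − 1.96). For n = 66 it is Φ(2.298 − 1.960) = Φ(0.338) = 63%. The t-based values are:

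| Per arm | Basis | Power, d = 0.4 |
|---|---|---|
| 66 | stated requirement | 63% |
| 75 | 100 less 25% | 68% |
| 80 | 100 less 20% | 71% |

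The smallest effect detectable at 90% power with 75 per arm is √(2 × 10.507/75) = 0.53.

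**Weight.** If 10% is an SD, d = 5/10 = 0.5.
- Two-group n = 2 × 10.507/0.25 = 84.1, so 85; t-based 86. After 25% attrition: 86/0.75 = 114.7, so 115.
- Power (t-based) is 56% with 37 per group, 86% with 75 and 88% with 80.
- If 10 is read literally as a variance in squared percentage points, the SD is 3.16% and n = 2 × 10.507 × 10/25 = 8.4, so 9 per group. Neither reading gives 37.

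**FFM.** If the 35% applies to the 5% weight difference, the FFM difference is 0.35 × 5% = 1.75% of body weight. The two-group n then depends wholly on an SD that is not stated. By the normal approximation:

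| Assumed SD (% of body weight) | n per group |
|---|---|
| 1.75 | 22 |
| 2.5 | 43 |
| 3.5 | 85 |
| 5 | 172 |

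An SD of about 2.5% makes 44 a correct two-group figure (t-based). The figure 44 is also the one-sample t-test n at d = 0.5 (43.995), but the section never assigns that effect size to FFM.

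**Attrition.** 37/0.75 = 49.3, so 50, not 48. 44/0.75 = 58.7, so 59, not 58. 66/0.75 = 88, as stated.

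**Baseline adjustment.** Adjusting for baseline multiplies the two-group n by (1 − ρ²).
- To bring 133 down to 66: ρ = √(1 − 66/133) = 0.71. To bring 86 down to 37: ρ is about 0.75.
- For 75 per arm to give 90% power at d = 0.4: ρ = √(1 − 75/133) = 0.66. At d = 0.5: ρ = √(1 − 75/86) = 0.36.

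**The case against.** The best defence is that the planned analysis uses four visits and allows covariance adjustment, so the smaller numbers may rest on a variance reduction set out in a fuller document. That is possible, and for this reason the use of a one-sample formula is an inference from the match at 65.7, not something the article says. It does not rescue the text as written. The section gives d = 0.4 with no correlation, covariance adjustment is planned only where confounding calls for it, and 66 and 37 need different correlations (about 0.71 and 0.75).

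A second defence is that 200 women are recruited, not 74 or 132, and that CD4 and viral load are not among the outcomes named as primary. Both points stand. They keep the shortfall on weight to 2–4 percentage points and confine the serious loss to CD4 and viral load. They do not correct the stated 66.

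A reader might go further and infer that all three figures are about half of what is needed. The article does not support that. The 44 for FFM cannot be tested without an SD and would be right at about 2.5% of body weight, and the error in 37 depends on reading 10% as an SD.

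A reader might also see a contradiction between 25% attrition here and the statement in Dietary intake study that "a drop-out rate of 20% is anticipated". The 25% is conditional and can be a planning margin above the expected rate, so this is not a clear conflict.

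**Conclusion.** The stated 66 per group for d = 0.4 is wrong as written for a two-group comparison. The requirement is 133 per group before loss and 178 after 25% attrition. This assumes a two-sided test at 0.05 with no baseline adjustment; a one-sided test would still need 108. The planned 200 women give about 68–71% power for CD4 and viral load at d = 0.4.

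The weight figure of 37 is also too low, against 86, if 10% is an SD. The trial as planned nevertheless has 86–88% power there, so the documents do not support a conclusion that it is seriously underpowered for weight. The FFM figure is not reproducible, which is different from being wrong. The attrition slips of one or two women per group are minor.

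**What to change.** Keep 200 women and revise the Sample size calculation section as follows.

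- State the sidedness of the test.
- Replace 66 with 133 per group for d = 0.4, and 88 with 178 after 25% loss.
- State the 10% for weight as an SD, if that is what is meant, and replace 37 with 86 per group (115 after 25% loss).
- Report the power that 200 women give: about 68–71% for CD4 and viral load at d = 0.4, and 86–88% for weight at d = 0.5, with 75–80 completers per arm.
- Give the FFM difference and SD behind 44, or recompute that line. If 44 stays, inflate it to 59.
- If a baseline-adjusted analysis is relied on, state the assumed correlation. With 75 per arm, 90% power needs about 0.36 at d = 0.5 and about 0.66 at d = 0.4.

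The cost is a rewritten section and a less favourable power statement. Recruitment does not change.

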### Statistical Analysis plan

Statistical analyses will be performed using SAS software (SAS Institute, Cary, NC, USA). Descriptive statistics will be provided for the nutritional status, body composition, clinical and socio-demographic characteristics of the participants at baseline, 4, 8 and 12 months follow-up. At baseline, the characteristics of participants on food supplement and those without food supplement will be compared using t-test for continuous variables and Fisher's Exact Test for categorical variables. Repeated measures analysis of variance (RM-ANOVA) will be employed to compare the primary outcome variables (nutritional status and body composition) in participants with and without food supplements. Where confounding variables may need to be account for, adjustment will be made by covariance.

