## Methods/Design

### Study design

This is a community-based controlled and longitudinal study. The study population will be comprised of HIV-infected females commencing ARV treatment at two Lusaka Urban clinics, Matero Reference Clinic (MRC) and Matero Main Clinic (MMC). The study participants will be allocated to either the experimental group and receive HEPS or control group and not receive HEPS. Participants will be randomly assigned to either group by the sister-in-charge at each clinic. Data will be collected at four time points across the 12-month study: baseline (0 months), 4-months, 8-months and 12-months follow-up. The study protocol has been approved by the University of Zambia Research Ethics Committee (approval ref 017-02-07).

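### RM-ANOVA is the named primary method, yet neither of its standard tests is aimed at the 12-month group difference on which the trial is sized

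*Protocol article*

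**What the plan says.** The Statistical Analysis plan section names one method for the main between-group comparison: "Repeated measures analysis of variance (RM-ANOVA) will be employed to compare the primary outcome variables", which it identifies as nutritional status and body composition. It does not say which RM-ANOVA term is the test, or whether baseline is a response or a covariate.

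Adjustment is conditional and tied to confounding: "Where confounding variables may need to be account for, adjustment will be made by covariance". The outcome's own baseline value is not mentioned. The software is SAS, with no procedure named.

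Three other sections bear on this choice:

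- Sample size calculation says the trial size was "based on detecting a 5% weight change between groups over the 12-month period". It then inflates each group size with the phrase "If the attrition is 25% over the year".
- Study design counts baseline as a time point: "Data will be collected at four time points across the 12-month study: baseline (0 months), 4-months, 8-months and 12-months follow-up".
- Allocation to study groups puts baseline measurement before the draw: "On the day of recruitment (baseline) after completing all body composition assessments and physical examination, the sister-in- charge will cut pieces of papers".

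The Dietary intake study section expects a 20% drop-out from 200 women.

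**The concern.** The quantity of interest is the difference between groups at 12 months. A four-visit RM-ANOVA has two standard tests that involve group, and neither is that contrast. The group main effect averages over all visits, including one taken before anyone is allocated. The group-by-time test asks whether the two profiles differ in any way. It has 3 degrees of freedom and does not by itself give a 12-month estimate.

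Neither test uses the baseline value as a covariate, although it is collected on every woman and is probably strongly related to later weight and fat-free mass.

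There is also a conditional issue. Classical RM-ANOVA needs a complete series from each woman, and the protocol expects to lose a fifth to a quarter of participants. The Determination of TBW section adds gaps by excluding out-of-range body-water values. What is at stake is power, a clear primary estimate and, if dropout is outcome-related and differs by arm, bias.

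**Working it through.** The protocol gives no power figure for RM-ANOVA, so there is no stated result to reproduce. The check compares the candidate tests under common inputs.

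**Inputs from the protocol**
- Effect of 5% of weight at 12 months. The stated 10% variance is read as an SD of 10%, so d = 5/10 = 0.5.
- 200 women allocated half and half, so 100 per arm. With 25% loss, n = 75 completers per arm.
- Alpha 0.05, taken as two-sided.
- Visits at 0, 4, 8 and 12 months, with an expected group difference of 0 at baseline.

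**Assumptions not in the protocol**
- Baseline-to-12-month correlation ρ of 0.5, 0.7 or 0.9.
- Covariance either compound-symmetric (CS, equal correlations) or autoregressive (AR).
- Effect either linear in time or full from month 4.

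**Step 1: what the group main effect estimates**
- Linear: (0 + 1/6 + 1/3 + 1/2)/4 = 0.25 SD, which is 50% of the 12-month effect.
- Full from month 4: (0 + 0.5 + 0.5 + 0.5)/4 = 0.375 SD, which is 75%.

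**Step 2: power of the main effect**

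Under CS, SE = √[(2/n)(1 + 3ρ)/4]. At ρ = 0.5 this is √[(2/75)(0.625)] = 0.129. The linear effect gives 0.25/0.129 = 1.94 and power of about 49%.

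**Step 3: power of group-by-time**

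Under CS, the noncentrality is λ = (n/2) Σ(δ_t − mean δ)² / (1 − ρ). For the linear effect the sum of squares is 2(0.25² + 0.0833²) = 0.139. At ρ = 0.5, λ = 37.5 × 0.139/0.5 = 10.4. On 3 and 146 degrees of freedom, power is about 77%. The AR structure gives 72%.

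**Step 4: power of the baseline-adjusted 12-month contrast, completers only**

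SE = √[(2/n)(1 − ρ²)]. At ρ = 0.5 this is √[(2/75)(0.75)] = 0.141. Then 0.5/0.141 = 3.54 and power is about 94%.

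**Step 5: ranges over all correlations and both structures**

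| Test | Linear effect | Full from month 4 |
|---|---|---|
| Group main effect | 34-49% | 65-82% |
| Group-by-time, 3 df | 72-100% | 89-100% |
| Baseline-adjusted 12-month contrast, completers | 94% or more | 94% or more |
| Likelihood repeated-measures model, partial data kept | 94.5% or more | 94.5% or more |

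**Step 6: cost of deleting incomplete series**

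Complete-case analysis would keep 200 × 0.80 = 160 or 200 × 0.75 = 150 women. Keeping partial data lowers the standard error of the 12-month contrast only slightly. At ρ = 0.5 (CS) it falls from 0.1414 to 0.1396, about 1%. At ρ = 0.9 (AR) it falls from 0.0712 to 0.0679, about 5%.

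**Step 7: bias from dropout (simulation, true effect 0.50 SD)**
- Dropout driven by the month-8 value in the same way in both arms: completers show 0.50, so no bias.
- Dropout that differs by arm: the raw 12-month difference in completers is 0.37-0.40, the baseline-adjusted completer difference is 0.44-0.48, and the difference in change is 0.48-0.49. The likelihood analysis using all visits gives about 0.50.

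Baseline adjustment alone therefore does not remove this bias. Using the partial series does.

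**The case against.** The strongest reply is that the article names a method and leaves its details to a fuller document. A reader might infer that the plan dilutes the effect and discards women lost to follow-up. The text supports neither as fact. It does not say that baseline is a response, that the main effect is the test, or that complete series are required, and SAS can fit repeated measures by likelihood with partial data. That stands.

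The reply also has force on the numbers:

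- Group-by-time is the usual test of a difference in change and is not diluted. If the effect is full from month 4 it can beat the 12-month contrast: with AR covariance and ρ = 0.5 it has 98.7% power against 94.0%.
- A plain two-sample t-test at 12 months with 75 per arm has about 86% power at d = 0.5.
- The large dropout bias belongs to the raw completer difference. A change contrast stays at 0.48-0.49, and equal dropout mechanisms give no bias.
- Nothing in the protocol shows that any particular kind of woman is more likely to leave. It shows only that contact differs: the supplement group collects food monthly with transport money, while the control group receives goods every 4 months.

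What the reply does not remove is that RM-ANOVA is a stated choice. Covariance adjustment is offered only for possible confounders, and neither standard test is the baseline-adjusted 12-month contrast.

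**Conclusion.** The point holds in a limited form. The protocol fixes a method whose standard tests do not match the 12-month difference used to size the trial, and a better-aimed method is available from the same data.

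The group main effect would be a poor choice, at 50-75% of the 12-month effect. Group-by-time is acceptable but unfocused. For a linear effect its power is 72-100%, against at least 94%, with the gap widest when visits are weakly correlated and closing as the correlation approaches 0.9. These figures rest on d = 0.5, 100 per arm, 25% loss, and correlations and effect shapes that the protocol does not give.

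Deletion of incomplete series is a risk only if RM-ANOVA is run in its classical form. Its precision cost is about 1-5% of the standard error. Bias matters mainly if outcome-related dropout differs by arm. This is an improvement that should be made, not evidence that the planned analysis is invalid.

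**What to change.** In the Statistical Analysis plan section, replace RM-ANOVA with a likelihood-based linear mixed model for repeated measures in SAS:

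- Outcomes: the 4-, 8- and 12-month values.
- Terms: group, visit, group × visit, baseline value and baseline × visit.
- Covariance: unstructured across visits.
- Data: all available visits, with no requirement for a complete series. A woman with no follow-up value contributes nothing to this model, and the text should say so.
- Primary contrast: the group difference at 12 months, with its confidence interval.

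State that baseline adjustment is planned in advance and does not depend on a judgement about confounding. The data and software are unchanged, and the cost is a rewritten paragraph.
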